## Abstract

**Background:**

Individuals with a unilateral severe-to-profound hearing loss, or single-sided deafness, report difficulty with listening in many everyday situations despite having access to well-preserved acoustic hearing in one ear. The standard of care for single-sided deafness available on the UK National Health Service is a contra-lateral routing of signals hearing aid which transfers sounds from the impaired ear to the non-impaired ear. This hearing aid has been found to improve speech understanding in noise when the signal-to-noise ratio is more favourable at the impaired ear than the non-impaired ear. However, the indiscriminate routing of signals to a single ear can have detrimental effects when interfering sounds are located on the side of the impaired ear. Recent published evidence has suggested that cochlear implantation in individuals with a single-sided deafness can restore access to the binaural cues which underpin the ability to localise sounds and segregate speech from other interfering sounds.

**Methods/Design:**

The current trial was designed to assess the efficacy of cochlear implantation compared to a contra-lateral routing of signals hearing aid in restoring binaural hearing in adults with acquired single-sided deafness. Patients are assessed at baseline and after receiving a contra-lateral routing of signals hearing aid. A cochlear implant is then provided to those patients who do not receive sufficient benefit from the hearing aid. This within-subject longitudinal design reflects the expected care pathway should cochlear implantation be provided for single-sided deafness on the UK National Health Service. The primary endpoints are measures of binaural hearing at baseline, after provision of a contra-lateral routing of signals hearing aid, and after cochlear implantation. Binaural hearing is assessed in terms of the accuracy with which sounds are localised and speech is perceived in background noise. The trial is also designed to measure the impact of the interventions on hearing- and health-related quality of life.

**Discussion:**

This multi-centre trial was designed to provide evidence for the efficacy of cochlear implantation compared to the contra-lateral routing of signals. A purpose-built sound presentation system and established measurement techniques will provide reliable and precise measures of binaural hearing.

**Trial registration:**

Current Controlled Trials http://www.controlled-trials.com/ISRCTN33301739 (05/JUL/2013)

## Background

Permanent acquired unilateral severe-to-profound hearing loss, or single-sided deafness (SSD), has been estimated to affect between 12–27 individuals in every 100,000 of the general population with the majority of losses being sudden and idiopathic; that is, a cause has not or cannot be determined [1]. Other aetiologies which may give rise to SSD include Vestibular Schwannoma (and associated surgery) and Ménière’s disease. Despite having normal or near-normal hearing in one ear, individuals with SSD report difficulty when listening in many everyday situations [2,3]. In particular, patients report disability when localising sounds and listening to sounds on the side of the impaired ear [4]. Compatible with these self-reported difficulties, individuals with SSD show little or no ability to localise sounds [5-8] and display a poor ability to understand speech in noise when the speech is on the impaired side of the head [5,6]. Both impairments reflect a lack of access to binaural cues such as inter-aural time and level differences, while the latter impairment also reflects the acoustic shadow cast by the head which attenuates the high-frequency components of sounds at the ear contra-lateral to their source.

In the UK National Health Service (NHS), the standard of care for SSD is a Contra-lateral Routing of Signals (CROS) hearing aid system. A CROS system picks up sounds arriving at the impaired ear using a remote microphone and presents those sounds to the non-impaired ear through a wired or wireless link [9]. The primary function of the system is therefore to overcome the acoustic shadow cast by the head and, in doing so, to improve access to sounds on the impaired side. The use of a CROS system has been found to improve the perception of speech in noise compared to the unaided condition when the most favourable signal-to-noise ratio is available at the impaired ear; i.e. with speech on the impaired side and the noise from the front [6,10,11] or speech from the front and noise on the non-impaired side [7,12,13]. Use of a CROS system has also been associated with a reduction in self-reported difficulty with background noise, communication, and reverberation [1]. However, the indiscriminate routing of sounds from the impaired ear to the non-impaired ear can produce undesirable results. For example, the perception of speech in noise can degrade with CROS use compared to the unaided condition when a background noise is located on the impaired side [6,11,13]. The use of a CROS has also been found to have no effect on localisation accuracy [6,10,11] which is compatible with the fact that the device is not designed to restore access to the binaural cues which underpin the ability to locate sounds in space. Finally, patients also report dissatisfaction with the requirement to wear a hearing aid device on their non-impaired ear [12,14].

Alternatives to a CROS include a Bone-Anchored Hearing Device (BAHD) which also transmits sounds arriving on the impaired side to the non-impaired ear but achieves this by conduction through the cranial bones. There is some emerging evidence that BAHD may provide benefits to speech perception in noise over a CROS system although more high quality trials are needed [1,15]. BAHD is currently only commissioned in the NHS in cases of profound unilateral sensorineural hearing loss where conventional acoustic aiding (such as with a CROS) is not possible or contra-indicated [16]. Like the CROS, a BAHD does not restore binaural hearing in individuals with SSD for whom the sensorineural component of the hearing loss is severe-to-profound. Poor localisation ability has been cited by patients as a factor which contributes to their decision not to receive a BAHD, as have cosmetic concerns about the placement of a permanent bone-anchored abutment through the skin [17].

An alternative treatment for SSD which does have the potential to restore access to binaural cues is cochlear implantation. In cases of SSD where the auditory nerve is intact, impairments of the middle and inner ear can be bypassed and the auditory nerve stimulated electrically. Like CROS and BAHD devices, cochlear implantation in SSD has been found to improve access to sounds on the impaired side and has been associated with a reduction in self-reported difficulties with listening to speech in noise [5,18,19]. Unlike CROS and BAHD devices, cochlear implantation has also been found to improve the accuracy with which sounds can be localised [5,18,19]. Thus, the restoration of input to the impaired ear has the capacity to provide access to the inter-aural cues which support localisation and to restore useful aspects of binaural hearing. The intervention therefore has the potential to alleviate the high-levels of difficulty that individuals with SSD report with understanding speech in many everyday situations containing background noise [4] and, in doing so, may improve their health-related quality of life [20].

In the NHS, cochlear implantation is currently commissioned for adults and children with bilateral severe-to-profound deafness [21] and is not commissioned routinely for individuals with SSD. Providing a cochlear implant in cases of SSD and supporting its effective use throughout the lifespan is likely to incur a substantially greater cost to the NHS compared to the provision and maintenance of the current standard of care, a CROS system. A cochlear implant is also a lifetime commitment and involves a surgical procedure whereas a CROS system is no more permanent or invasive than a conventional acoustic hearing aid. For these two reasons, it was anticipated that cochlear implantation would be unlikely to be considered as an *alternative* to CROS in the NHS. Rather, it may be considered as an intervention for SSD in cases where a CROS system has been found to offer insufficient benefit as in these cases no other treatment options are currently available on the NHS. The current trial was therefore designed to evaluate whether cochlear implantation provides benefit to those patients who report receiving insufficient benefit from a CROS system.

### Purpose

This within-subjects longitudinal trial will determine whether cochlear implantation provides significant benefit in patients who have failed to receive sufficient benefit from a Contra-lateral Routing of Signals (CROS) system.

### Primary objectives

• Does a cochlear implant significantly improve sound localisation compared to a CROS hearing aid in patients who report insufficient benefit from a CROS?

• Does a cochlear implant significantly improve speech perception in noise compared to a CROS hearing aid in patients who report insufficient benefit from a CROS?

### Secondary objective

• Does a cochlear implant significantly improve quality of life compared to a CROS hearing aid in patients who report insufficient benefit from a CROS?

## Methods/Design

The trial is a within-subjects longitudinal study in which participants will be assessed before and after receiving two interventions delivered in a fixed order. Participants will be recruited from five NHS Trusts in the UK: (1) Nottingham University Hospitals NHS Trust; (2) University Hospitals Birmingham NHS Foundation Trust; (3) Central Manchester University Hospitals NHS Foundation Trust; (4) University College London Hospitals NHS Foundation Trust; and (5) Guy’s and St. Thomas’ NHS Foundation Trust. The trial is being coordinated by the National Institute for Health Research (NIHR) Nottingham Hearing Biomedical Research Unit, Nottingham. After screening against the inclusion/exclusion criteria, participants will progress through three phases: baseline, CROS, and cochlear implantation (Figure 1). During the two-month baseline phase, participants receive no treatment; in the CROS phase, participants will be fitted with a CROS system and complete a 3-month trial of the device; in the cochlear implantation phase participants will receive a cochlear implant and follow-up will continue for 9 months.

**Figure 1 F1:**
[figure not shown]
**Trial design.** A schematic representation of the sequence and timing of appointments that each participant will complete divided into the three trial phases. In the baseline phase, participants will use no hearing-assistive device and the listening tests will be administered during the two-month delay between baseline questionnaire assessments. After both CROS and cochlear implant fitting, participants will complete a daily diary to track device usage and to capture any comments on the advantages/disadvantages of the devices. CROS: Contra-lateral Routing of Signals.

The duration of the CROS trial (3 months) was chosen in consultation with clinical colleagues from several UK audiology services to ensure that (a) it was of sufficient duration to allow the benefits from CROS to emerge; (b) any benefits from CROS would have stabilised; and (c) self-reported benefits would be based on patients’ experience of CROS use rather than any pre-conceived expectations (whether positive or negative). The duration of the cochlear implantation follow-up period (9 months) was chosen based on data from previous studies which have observed that (a) a large proportion of the benefit from cochlear implantation is achieved within the first 9 months and additional benefits emerge at a slower rate over the course of several years [22,23]; and (b) significant benefits to binaural hearing from cochlear implantation in patients with SSD can be achieved as early as 6 months after implantation [5].

The primary endpoints are the assessments of sound localisation and speech understanding in noise at baseline, after CROS aiding, and after cochlear implantation. Secondary endpoints are questionnaire measures of hearing- and health-related quality of life and the impact of tinnitus at baseline, after CROS aiding, and after cochlear implantation.

The trial protocol and the study activities across the five NHS trusts were given a favourable opinion by the National Research Ethics Committee, East Midlands Nottingham - 2, Nottingham, UK (12/EM/0378). The sponsor of the trial is Nottingham University Hospitals NHS Trust, Research and Innovation Department, Nottingham, UK.

### Population and sample size

Participants will be recruited from a notes review at each of the participating hospitals. The primary outcome measure is sound localisation accuracy; specifically, the mean absolute angular error in localising speech sounds. The trial is powered to detect a within-subject improvement in mean localisation accuracy resulting from the use of a cochlear implant compared to, and following the use of, a Contra-lateral Routing of Signals (CROS) hearing aid. A previous study examined the within-subject improvement in localisation accuracy after cochlear implantation compared to brief periods of CROS and simulated BAHD use prior to implantation [5]. The authors reported localisation performance after 3-week trials of both a CROS aid and a BAHD on a soft band (without a permanent bone-anchored abutment), completed in a random order. They subsequently reported localisation performance data obtained 6 months after participants had received a cochlear implant.

Arndt et al. [5] reported the median, range, and inter-quartile range of localisation performance at the end of the follow-up period for each device. Standard deviations for the localisation performance data after 3 weeks of CROS use and after 6 months of cochlear implant use were estimated from the inter-quartile ranges [24]. As only summary statistics were available, the correlation between the CROS (i.e. pre-cochlear implant) and post-cochlear implant measures could not be determined. The data were assumed to be uncorrelated yielding an estimated effect size of 1.63 standard deviations. To detect an effect of this magnitude using a one-tailed Wilcoxon signed-rank test at *α*=0.05 and with 95% power would require a sample size of 7. A final sample size of 10 was chosen to achieve the desired statistical power and to allow for some attrition due to the length of the follow-up period after cochlear implantation (9 months). The desired power reflects the fact that a study of this nature is unlikely to be repeated due to the substantial cost of providing the participants with a cochlear implant.

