### Primary outcome measures

Assessments of the ability to localise sounds and understand speech in noise will be administered using a purpose-built test setup [28-30] in an anechoic chamber at the MRC Institute of Hearing Research in Nottingham.

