#### *Sound localisation*

Sound localisation will be measured in anechoic conditions and a range of reverberant conditions following established methods using a visual-pointing technique [31]. On each trial, a short pre-recorded speech segment will be presented from one of several loudspeakers positioned in the frontal plane and behind an acoustically-transparent curtain (Figure 3). Speech segments will be short isophonemic words [32] spoken by a male talker with a British accent. The task of participants will be to indicate the perceived location of the sound by moving a visual pointer projected onto the curtain. The position of the visual pointer will be adjusted using a computer-controlled trackball mouse and with a precision exceeding one degree of visual angle. Presentation levels will be roved from trial to trial to restrict the use of monaural loudness cues and limited so that stimuli do not engage the compression features of the cochlear implant sound processor which can degrade inter-aural level cues [33-35].

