#### *Speech understanding in noise*

Speech understanding in noise will be measured in terms of a speech-reception threshold (SRT) which represents the signal-to-noise ratio (SNR) at which 50% of sentences are reported correctly. Sentences will be drawn from a recording of the IEEE sentence corpus [36] spoken by a female talker with a British accent. The masking noise will be generated to match the long-term average spectrum of the sentences. SRTs will be measured using an adaptive procedure to avoid floor and ceiling effects by varying the level of the speech and noise from trial to trial based on the accuracy with which the participant recalls keywords in the sentences [37]. The spatial configuration of the speech and the noise will be varied across testing conditions to estimate the three main effects of two-eared listening to speech in noise [38]: i) the head-shadow effect estimated from the test conditions in which the speech is positioned on the side of the impaired ear and the noise is on the side of the non-impaired ear; ii) binaural squelch effect estimated from the test conditions in which the noise is positioned on the side of the impaired ear and the speech is on the side of the non-impaired ear; iii) binaural summation (redundancy) effect estimated from the test conditions in which the speech and noise are positioned equidistant from both ears; i.e. directly in front of the participant. SRTs will be reported for each individual participant along with a measure of the variance of the SNRs used to compute each SRT.

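### The protocol names one primary outcome where it sizes the trial but two elsewhere; only localisation was sized, and its deciding test condition is not named

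*Protocol article*

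**What the plan says.** Population and sample size names a single measure: "The primary outcome measure is sound localisation accuracy; specifically, the mean absolute angular error in localising speech sounds". It sizes the trial on that measure: an effect of 1.63 SD, a one-tailed Wilcoxon signed-rank test at α = 0.05 and 95% power give 7 participants, raised to 10 for attrition.

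Four other places give two outcomes equal standing:

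- Methods/Design, in the text after the Figure 1 legend: "The primary endpoints are the assessments of sound localisation and speech understanding in noise at baseline, after CROS aiding, and after cochlear implantation".
- Primary objectives, where the second of two questions reads: "Does a cochlear implant significantly improve speech perception in noise compared to a CROS hearing aid in patients who report insufficient benefit from a CROS".
- Abstract, Methods/Design paragraph, which has plural primary endpoints and explains them thus: "Binaural hearing is assessed in terms of the accuracy with which sounds are localised and speech is perceived in background noise".
- Primary outcome measures, whose opening sentence covers both tests: "Assessments of the ability to localise sounds and understand speech in noise will be administered using a purpose-built test setup".

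The Efficacy analysis section refers to a primary endpoint in the singular, but fixes only its time point (9 months after implantation) and not the outcome.

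On test conditions, the Sound localisation section says: "Sound localisation will be measured in anechoic conditions and a range of reverberant conditions following established methods". For speech, "The spatial configuration of the speech and the noise will be varied across testing conditions", which gives speech-reception thresholds (SRTs) in three arrangements (head shadow, squelch, summation).

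**The concern.** What is primary is a matter for the protocol itself, and here it has two answers. Under the sizing text, a trial that succeeds on speech but not on localisation has missed its primary outcome. Under the other four sections it has met one of two primary objectives. Both readings would be available once the data are known.

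The same freedom exists within localisation, because the sizing text names an error measure but not the listening condition in which it decides the comparison.

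For speech, the arrangement could matter to the answer. The Background reports that a CROS aid helps when the better signal-to-noise ratio is at the impaired ear and can harm when noise is on the impaired side. The comparator may therefore perform quite differently in the head-shadow and squelch arrangements.

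If both outcomes are primary, one of them also has no stated effect size or power. The protocol justifies its high power by saying that the study is unlikely to be repeated, so it is worth being clear about which objective that power serves.

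**Working it through.** **1. The protocol's own sample size.** Inputs from Population and sample size: effect 1.63 SD, one-sided α = 0.05, target power 95%, Wilcoxon signed-rank test. Approximate the Wilcoxon test by a paired t-test with effective size m = n × 3/π (normal differences):

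Power = 1 − F(t₀.₉₅; df = m − 1, noncentrality = 1.63 × √m), with F the noncentral t distribution and t₀.₉₅ the central-t critical value.

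- n = 6: power 94.9%. Simulation of the exact signed-rank test gives 94.5%. Both are just short of 95%.
- n = 7: m = 6.68, critical value 1.963, noncentrality 4.214, power 97.8% (exact test 96.8%).

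So 7 is the smallest size that reaches 95%. The figure reproduces, for one localisation comparison.

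**2. False primary success if either outcome counts.** Assumptions, not in the document: one test per outcome, each at the sizing level of one-sided 5%, and success on either is enough.

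- Independent tests: 1 − 0.95² = 0.0975, or 9.75%.
- Correlation 0.5 (bivariate normal): 1 − Φ₂(1.645, 1.645; 0.5) = 0.0878, or about 8.8%.
- If each of the three SRT arrangements were also a separate route to success (four tests): 1 − 0.95⁴ = 0.185, or 18.5%, with independence, and 14.4% at correlation 0.5.
- If both outcomes had to succeed, there would be no inflation. The document does not state that rule either.

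**3. What the sample can detect for speech.** No speech effect is given, so solve the formula in step 1 for the effect, at one-sided 5%:

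| Pairs | Effect for 80% power | Effect for 95% power |
|---|---|---|
| 10 | 0.88 SD | 1.16 SD |
| 7 | 1.10 SD | 1.46 SD |

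The other way round, with 10 pairs, over an assumed range of true effects: 0.5 SD gives 41% power, 0.8 SD gives 73%, 1.0 SD gives 88% and 1.2 SD gives 96%.

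**4. Cost of keeping two primaries with alpha split.** At one-sided 0.025 and 1.63 SD, localisation has 99.3% power with 10 pairs and 93.1% with 7. Speech with 10 pairs falls to 28% at 0.5 SD, 59% at 0.8 SD and 78% at 1.0 SD.

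**The case against.** The strongest reply has four parts.

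- **Multiplicity rules may be elsewhere.** This is a condensed article, and an alpha split, a hierarchy or an adjustment method could sit in the full protocol or the analysis plan. That stands: their absence here is not the finding. It does not answer the contradiction, because the article does define the primary outcome and does so in two incompatible ways.
- **The error rates are conditional.** One-tailed 5% appears only in the sizing calculation. The Efficacy analysis section gives no level or sidedness, and it allows a repeated-measures analysis of variance, which could cover several conditions in one test. That stands too, so 9.75% is an illustration under stated assumptions. A reader might infer a much higher rate by counting every SRT arrangement and every reverberant condition as a separate primary test. The document does not support that. It gives no number of reverberant conditions and uses them to find how much reverberation participants tolerate. It uses the speech arrangements to estimate three distinct effects.
- **The scope of the power is disclosed.** Both the sizing section and the Sound localisation section tie the power to localisation data. A reader might infer that the protocol claims 95% power for speech, but it does not. The effects in step 3 do not show a shortfall either, since there is no speech effect to set them against.
- **Localisation is robust.** Even at one-sided 0.0125, 10 pairs keep about 97 to 98% power at 1.63 SD. This stands, and it means that resolving the contradiction costs the main comparison little or nothing.

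**Conclusion.** The point holds as an internal contradiction. One section names a single primary outcome and sizes the trial on it; four others make speech in noise equally primary. The localisation measure is also not tied to a listening condition. Followed as written, there are two primary routes to success, and only one has a sizing basis.

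On the either-outcome reading, the false-success risk is roughly double the nominal 5%: 9.75% if independent and about 8.8% at correlation 0.5. This assumes one one-sided 5% test per outcome. It reaches 18.5% only if all three SRT arrangements count separately and the tests are independent.

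Power for speech is unknown rather than shown to be inadequate. With 10 pairs, it reaches 80% only if the true paired effect is about 0.88 SD or more.

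The sample-size arithmetic is correct and is not in question. The power figures here rest on normally distributed differences and, for localisation, on the protocol's 1.63 SD.

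**What to change.** **Preferred.** Keep one primary outcome, the one on which the trial was sized: mean absolute localisation error in one named condition (for example anechoic), cochlear implant at 9 months against CROS at 3 months. Make speech in noise a key secondary outcome, tested only if localisation is significant, with the three SRT arrangements adjusted among themselves (for example by Holm). Treat reverberant localisation as descriptive. Reword the Abstract, Primary objectives, Methods/Design and Primary outcome measures to match, and say there that speech was not powered.

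**Cost.** No added participants, visits or tests, and localisation keeps its full alpha and power. It is more than a wording change, though: speech loses its equal primary status, and no confirmatory claim could be made for it if localisation failed.

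**Acceptable alternative.** If the sponsor wants two primaries, state so in the sample-size section and split alpha at one-sided 0.025 each. Name the localisation condition, and say how the SRT arrangements share the speech portion. Localisation keeps about 99% power with 10 pairs at 1.63 SD. The price is lower power for speech, as in step 4.

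The trial is reported as still recruiting, so either choice can be recorded before the 9-month comparison is analysed.
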